| 2.2.2 Drop-out criteria           | 
Research personnel, the ethics committee, or associated institutions can consider drop-out of participants if it is necessary. Details are as follows:
 
 
- In case of failure to complete the first day procedure
 
- If participants do not follow instructions of research personnel
 
- When discontinuation of trial participation is optimal for a participant because he or she experiences an severe adverse event
 
                                                                                                                                                                                                                                                                                                                                                                                                                                                                 |
| 2.2.3 Termination of study        | 
Research personnel, the ethics committee, or associated institutions can decide the termination of study if it is necessary. Details are as follows:
 
 
- When the termination is optimal for participants because a number of severe adverse events occur.
 
- Other cases that need termination
 
                                                                                                                                                                                                                                                                                                                                                                                                                                                                                                                                                                                                 |

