| 2.2.6 Informed consent                                                  | 
 
- At the beginning of the study, one of the two informed consent forms that differently disclosed placebo information (fully disclosed vs. partially disclosed) will be randomly given to participants. They will be informed not the true hypothesis but alternative hypothesis of the study, i.e., to investigate the effect of acupuncture for this delayed onset muscle soreness.
 
- At the end of the study, the genuine study hypothesis will be debriefed to participants that this study is not to investigate the effect of acupuncture treatment for delayed muscle pain, but to examine the impact of the placebo information in informed consent form on the study results and blinding.
 
- Only data of participants who provide the written informed consent after debriefing will be subject to analysis.
 
                                                                                                                                                                                                                                                                                                                                                                                                                                                                                                         |

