
|                                                                               | 
for three consecutive days with manipulation (by rotating 180 degrees clockwise and counter-clockwise in a frequency of 2 Hz at immediately, 3, 6, 9, and 12 minutes after needle insertion)
 
3. After acupuncture treatment
 
 
- To fill out de-qi questionnaire
 
- Measurement of muscle discomfort in the non-dominant arm with VAS
 
- Measurement of PPT in the non-dominant arm
 
- To fill out acupuncture credibility Test
 
- Assessment of blinding effectiveness
 
 
4. Debriefing
 
 
- Debriefing to the type of acupuncture and informed consent form and interviewing about the other type of informed consent form
 
- Debriefing to the genuine study hypothesis and asking to participants whether the study design is acceptable and whether they can provide informed consent about the genuine study design and analysis their data
 
- Data of participants who decided not to provide written informed consent at the end of the study will not be analyzed.
 
 |      |         |                          |                                                                                                                                                            |

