| 2.3.10 Safety securing | 
 
- Monitoring adverse events
 
- Interviewing with participants at day 2 and day 3 visit
 
- Any adverse event will be described with details and numbers of adverse events have causal relationship or do not have one will be also described.
 
- Adverse events that are frequently reported following acupuncture: bruising, local pain, and minor bleeding (MacPherson, 2001)
 
- Adverse events refer to undesired and unintended signs (e.g., abnormalities in laboratory tests), symptoms, or diseases occurring after the treatment in the study. The events do not necessarily have a causal relationship with the treatment.
 
- Assessment of the severity (following Common Terminology Criteria for Adverse Events, CTCAE) 
 
✓ Grade 1 Mild; asymptomatic or mild symptoms; clinical or diagnostic observations only; intervention not indicated.
 
✓ Grade 2 Moderate; minimal, local or noninvasive intervention indicated; limiting age appropriate instrumental ADL*.
 
✓ Grade 3 Severe or medically significant but not immediately life-threatening; hospitalization or prolongation of hospitalization indicated; disabling; limiting self care ADL**.
 
✓ Grade 4 Life-threatening consequences; urgent intervention indicated.
 
✓ Grade 5 Death related to adverse event.
 
 
 
- Assessment of the causality (following WHO-UMC Causality Categories) 
 
✓ Certain
 
 
 
 |

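### Analysis requires consent given after a debriefing that is scheduled only at the end of Day 3, so anyone who leaves earlier cannot enter any analysis and is never told the genuine hypothesis

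*Protocol*

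**What the plan says.** The rule for whose data count appears in the summary (1.3.3) and again in 2.2.6: "Only data of participants who provide the written informed consent after debriefing will be subject to analysis". Section 2.2.6 also fixes the timing: "At the end of the study, the genuine study hypothesis will be debriefed to participants".

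In the visit schedules (1.4.2 and 2.3.4) debriefing is step 4 of the third visit and appears nowhere in the first two. It includes "Debriefing to the genuine study hypothesis and asking to participants whether the study design is acceptable" and the request for consent to use the data. A further line in the same step reads: "Data of participants who decided not to provide written informed consent at the end of the study will not be analyzed".

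There are several ways to leave before that step. Section 2.2.2 lists "In case of failure to complete the first day procedure", "If participants do not follow instructions of research personnel", and discontinuation because of a severe adverse event. Section 2.2.10 allows voluntary withdrawal at any time. None of these sections provides a debriefing or a second consent on exit.

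Section 2.2.4 recruits 89 to reach 80, allowing for 10% drop-out.

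**The concern.** A positive signature after debriefing is a condition for analysing any of a participant's data, and the only chance to give it comes after the last session. Leaving early therefore removes a person from the analysis without that person ever having refused.

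Three things are at stake.

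- **The randomised comparison.** The analysed set is defined by events after randomisation: staying to the end of Day 3 and then consenting. If leaving is related to the form received or to the needle, the four cells are no longer the groups that were randomised.
- **The adverse-event comparison.** Section 2.3.9 compares treatment-related adverse events between needle types. A participant withdrawn for a severe event before the end of Day 3 would, on a literal reading, not be counted in it.
- **The justification of the deception.** The background (2.1.3) treats withholding the true purpose as acceptable because participants are told at the end. Early leavers were given the alternative hypothesis and are not told.

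This is a stated rule combined with a stated schedule. A statistical analysis plan could not repair it alone, because the consent procedure decides whose data may be used.

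**Working it through.** **1. The plan's own figure.** Target 80, drop-out 10% (2.2.4): 80 / (1 − 0.10) = 88.9, rounded up to 89. The stated number is reproduced.

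**2. Who is lost.** 89 − 80 = 9 participants. With 89 / 4 = 22.25 per cell, that is about 2 per cell. This takes the 10% as exits before debriefing; the protocol does not say what the allowance covers. Refusals then come on top. If 5%, 10% or 20% of the 80 refused (assumed), 76, 72 or 64 would remain.

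**3. What early leavers would have contributed (counted from 2.3.4).**

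| Measure | When collected | Available after a completed Day 2 |
|---|---|---|
| Myers index, ABS, STAI-X | Day 1 | yes |
| VAS | 2 readings per day, 6 in all | 4 of 6 |
| PPT | 3 on Day 1, then 2 per day, 7 in all | 5 of 7 |
| De-qi questionnaire | each day | 2 of 3 |
| Acupuncture credibility test, blinding | end of Day 3 | no |

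The recoverable material is therefore mainly VAS, PPT and adverse events, plus the Day 1 questionnaires. Blinding is not recoverable.

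**4. Possible bias in the disclosure effect.** The protocol gives no loss rate by form and no SD, so this is an illustration. Suppose the form has no true effect. If a share d of a form's participants is lost and leavers differ from stayers by k SD, then

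mean of all = mean of stayers + d × k, so the stayers' mean is off by d × k.

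With the same k for both forms, the false difference is (d₂ − d₁) × k. The type I error uses a two-sided normal test at 0.05 (the protocol does not state sidedness), 44.5 randomised per form, and SE = √[1/(44.5(1 − d₁)) + 1/(44.5(1 − d₂))].

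| Loss by form (assumed) | k | False difference | Type I error |
|---|---|---|---|
| 10% vs 10% | 0.5 or 1 | 0 | 5.0% |
| 5% vs 15% | 0.5 | 0.10 × 0.5 = 0.05 SD | 5.6% |
| 5% vs 15% | 1 | 0.10 × 1 = 0.10 SD | 7.3% |
| 0% vs 20% | 0.5 | 0.20 × 0.5 = 0.10 SD | 7.3% |
| 0% vs 20% | 1 | 0.20 × 1 = 0.20 SD | 14.4% |

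For scale, the SE of the disclosure main effect at 80 analysed is √(1/40 + 1/40) = 0.224 SD.

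**5. One cell against the main effect.** Each form's mean averages two cells. A shift of 0.20 SD in a single cell therefore moves the main effect by 0.20 / 2 = 0.10 SD, under half a standard error.

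**The case against.** **No sentence says that early leavers are deleted.** The schedule is written for someone who attends every visit. That is true: the exclusion is an inference. But it follows directly from a rule that requires the signature and a schedule that offers it once.

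**A reader might infer that the protocol contains two contradictory rules.** The schedule line excludes those who decided against consent, and a person never asked has decided nothing. But that line sits inside the Day 3 debriefing step and concerns people who are present and asked. It is narrower than 2.2.6 and silent on early leavers, and both can be followed at once. The wording should be aligned; it is not a contradiction.

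**A reader might infer that safety information disappears.** Notification of serious events to the IRB (1.3.4), the narrative description of serious events (2.2.9) and the description of any adverse event (2.3.10) are not conditional on the second consent. What is exposed is the between-needle frequency test in 2.3.9.

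**A reader might infer a bias near one standard error.** That requires both cells of one form to lose 20% while the other form loses none, with leavers a full SD different. The documents support no such figure. With three consecutive days and payment per visit (2.2.8), loss may be small.

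**A reader might infer that refusal is driven by unmasking.** The debriefing step lists "Debriefing to the type of acupuncture and informed consent form and interviewing about the other type of informed consent form" ahead of the request for data consent. Refusal could depend on the cell, but nothing shows that it would. Taking consent before revealing the needle type would weaken the debriefing that justifies the deception, and disclosing the genuine hypothesis exposes the form manipulation anyway. I do not propose it.

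**The study is declared exploratory (2.2.4), and excluding debriefed refusers is proper.** Both points stand. The exclusion of refusers is a legitimate consequence of the deception and is not the defect.

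**Conclusion.** The concern holds in this form: followed literally, 2.2.6 and the schedule exclude everyone who leaves before the end of Day 3 from every analysis, the adverse-event comparison in 2.3.9 included, and leave them without debriefing. That is about 9 of 89 participants if the plan's 10% allowance is made up of such exits, before any refusals.

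The size of the bias is not known. It is zero when loss is equal across forms and leavers differ from stayers to the same degree under each. Under the assumed 5% against 15% loss it is 0.05 to 0.10 SD, with a type I error of 5.6% to 7.3%. These loss rates and the 0.5 to 1 SD difference are assumptions.

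The documents do not show that the four-cell comparison is invalid, that the two consent sentences conflict, or that adverse events go unreported. Early leavers would be absent from the Blinding Index under any consent rule, because blinding is assessed only after the third session. The debriefing gap remains whatever the size of the bias.

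**What to change.** 1. In 2.2.6, 2.2.2 and 2.2.10, offer debriefing and the data-consent form to every participant at the point of exit, on whatever day.
2. Use one rule in 1.3.3, 1.4.2, 2.2.6 and 2.3.4: all randomised, eligible participants who give data consent at exit or on Day 3 are analysed in their allocated cell, with all readings obtained. The word eligible matters because the form is handed out before Day 1 screening. Keep the exclusion of participants who are debriefed and refuse.
3. State that the adverse-event reporting in 1.3.4, 2.2.9 and 2.3.10 does not depend on that consent.
4. Report early exits and refusals by cell.

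The cost is protocol wording and, at the plan's own drop-out rate, about 9 extra debriefing conversations. No new sample size is needed. The gain is mainly VAS, PPT and adverse-event data. The downside is that some early leavers may not be reachable, so some loss will remain.

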|  | 
 
- To fill out Myers credibility index checking overall validity of informed consent document
 
- To fill out Acupuncture Belief Scale (ABS) and State-Trait Anxiety Inventory-X (STAI-X)
 
- To measure pressure pain phreshold (PPT) in the non-dominant upper arm
 
 
3. Induction of delayed onset muscle soreness model
 
 
- Measurement of 1 Repetition Maximum (1RM) in the non-dominant arm
 
- Repetitive arm-curl exercise in the non-dominant arm using 1RM weighted dumbbell
 
- Measurement of muscle discomfort in the non-dominant arm with visual analogue scale (VAS)
 
- Measurement of PPT in the non-dominant arm
 
 
4. Acupuncture treatment
 
 
- RA (PC2, LI4, LI11 and LU5 of the non-dominant arm) and PA (two points on the muscle belly of biceps brachii, 1 cun proximally from LI11, and 1 cun laterally from PC2 of the non-dominant arm) will be performed for 15 minutes once daily for three consecutive days with manipulation (by rotating 180 degrees clockwise and counter-clockwise in a frequency of 2 Hz at immediately, 3, 6, 9, and 12 minutes after needle insertion)
 
 
5. After acupuncture treatment
 
 
- To fill out de-qi questionnaire
 
- Measurement of muscle discomfort in the non-dominant arm with VAS
 
- Measurement of PPT in the non-dominant arm
 
 <hr/> 
1. Before acupuncture treatment
 
 
- Adverse event monitoring
 
- Measurement of muscle discomfort in the non-dominant arm with VAS
 
- Measurement of PPT in the non-dominant arm
 
 
2. Acupuncture treatment
 
 
- RA (PC2, LI4, LI11 and LU5 of the non-dominant arm) and PA (two points on the muscle belly of biceps brachii, 1 cun proximally from LI11, and 1 cun laterally from PC2 of the non-dominant arm) will be performed for 15 minutes once daily for three consecutive days with manipulation (by rotating 180 degrees clockwise and counter-clockwise in a frequency of 2 Hz at immediately, 3, 6, 9, and 12 minutes after needle insertion)
 
 
3. After acupuncture treatment
 
 
- To fill out de-qi questionnaire
 
- Measurement of muscle discomfort in the non-dominant arm with VAS
 
- Measurement of PPT in the non-dominant arm
 
 <hr/> 
1. Before acupuncture treatment
 
 
- Adverse event monitoring
 
- Measurement of muscle discomfort in the non-dominant arm with
 
 |

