| 1                                                                                                                                                                                                                                                                                                                                                                                                                                                                                                                                                                                                                                                                                                                                                                                                                                                                                                                                                                                       | 
1. Retrieval of written Informed consent
 
2. Screening
 
- Measurement of height and weight
 
- To check history of past/present illness, smoking/drinking, and resistance training
 
- To fill out Myers credibility index checking overall validity of informed consent document
 
- To fill out ABS and STAI-X
 
- To measure PPT in the non-dominant upper arm
 |                                                                                                                                                                                                                                                                                                                                                                                                                                                                                                                           |                          |                       |                    |           |                                                                                                                                                                                                                                                                                                                                                                                                                                      |                      |                                       |                      |                                      |          |                                                                     |             |                 |

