|  | 
 
3. Induction of delayed onset muscle soreness model
 
 
- Measurement of 1RM in the non-dominant arm
 
- Repetitive arm-curl exercise in the non-dominant arm using 1RM weighted dumbbell
 
- Measurement of muscle discomfort in the non-dominant arm with VAS
 
- Measurement of PPT in the non-dominant arm
 
 
4. Acupuncture treatment
 
 
- RA (PC2, LI4, LI11 and LU5 of the non-dominant arm) and PA (two points on the muscle belly of biceps brachii, 1 cun proximally from LI11, and 1 cun laterally from PC2 of the non-dominant arm) will be performed for 15 minutes once daily for three consecutive days with manipulation (by rotating 180 degrees clockwise and counter-clockwise in a frequency of 2 Hz at immediately, 3, 6, 9, and 12 minutes after needle insertion)
 
 
5. After acupuncture treatment
 
 
- To fill out de-qi questionnaire
 
- Measurement of muscle discomfort in the non-dominant arm with VAS
 
- Measurement of PPT in the non-dominant arm
 
 
 <hr/> 
 
1. Before acupuncture treatment
 
 
- Adverse event monitoring
 
- Measurement of muscle discomfort in the non-dominant arm with VAS
 
- Measurement of PPT in the non-dominant arm
 
 
2. Acupuncture treatment
 
 
- RA (PC2, LI4, LI11 and LU5 of the non-dominant arm) and PA (two points on the muscle belly of biceps brachii, 1 cun proximally from LI11, and 1 cun laterally from PC2 of the non-dominant arm) will be performed for 15 minutes once daily for three consecutive days with manipulation (by rotating 180 degrees clockwise and counter-clockwise in a frequency of 2 Hz at immediately, 3, 6, 9, and 12 minutes after needle insertion)
 
 
3. After acupuncture treatment
 
 
- To fill out de-qi questionnaire
 
- Measurement of muscle discomfort in the non-dominant arm with VAS
 
- Measurement of PPT in the non-dominant arm
 
 
 <hr/> 
 
1. Before acupuncture treatment
 
 
- Adverse event monitoring
 
- Measurement of muscle discomfort in the non-dominant arm with VAS
 
- Measurement of PPT in the non-dominant arm
 
 
2. Acupuncture treatment
 
 
- RA (PC2, LI4, LI11 and LU5 of the non-dominant arm) and PA (two points on the muscle belly of biceps brachii, 1 cun proximally from LI11, and 1 cun laterally from PC2 of the non-dominant arm) will be performed for 15 minutes once daily
 
 
 |

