| 2.3.9 Statistical plan | 
Main outcomes are pain outcomes and blinding of participants
 
 
- Pain outcomes: PPT and VAS.
 
✓ Two way ANOVA is considered as the way of statistical plan as it can analyze effect of two interventions (acupuncture and informed consent)
 
✓ The effect will be assessed as statistically significant when p value is under 0.05.
 
- Blinding of participants will be analyzed using a Blinding Index (BI, Bang, 2004).
 
- Scores of Myers credibility index, ABS, STAI-X, acupuncture credibility test, and de-qi questionnaire will be analyzed using two-way ANOVA with independent variables (type of acupuncture and placebo information disclosure). A p value less than 0.05 will be considered as statistically significant.
 
- Adverse events will be reported with details and causal relationship with acupuncture will be also assessed. Whether frequency of adverse events that has causal relationship with acupuncture differ between acupuncture types will be analyzed using chi-squared test or Fisher's exact test. A p value less than 0.05 will be considered as statistically significant.
 
- Demographic data will reported descriptively, i.e., continuous variables will be described with mean <math>\pm</math> standard deviation and categorical variables will be shown as frequency (%).
 
                                                                                                                                                                                 |

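### Three questionnaires completed before any needling (Myers index, ABS, STAI-X) are to be tested for an acupuncture effect that they cannot show; only the disclosure comparison has a meaning for them (minor)

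*Protocol*

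**What the plan says.** Section 2.3.9 (Statistical plan) fixes the analysis of the secondary questionnaires in one sentence: "Scores of Myers credibility index, ABS, STAI-X, acupuncture credibility test, and de-qi questionnaire will be analyzed using two-way ANOVA with independent variables", the variables being "type of acupuncture and placebo information disclosure". The criterion follows: "A p value less than 0.05 will be considered as statistically significant". All five scores are treated alike.

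Section 2.3.4 (Study schedule) gives the Day 1 order. Consent is step 1. Screening is step 2 and includes "To fill out Myers credibility index checking overall validity of informed consent document" and "To fill out ABS and STAI-X". Step 3 induces the muscle soreness, and the first needling comes only at "4. Acupuncture treatment". The summary schedule in section 1.4.2 has the same order ("To fill out Acupuncture Belief Scale (ABS) and State-Trait Anxiety Inventory-X (STAI-X"). Neither schedule lists these three questionnaires again, either after needling on Day 1 or on Days 2 and 3.

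The other two scores follow needling. The de-qi form ("To fill out de-qi questionnaire") is completed after each session, and the acupuncture credibility test after the Day 3 session. Section 2.2.6 says that one of the two consent forms is given at random at the beginning, so participants have met the disclosure factor before step 2.

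**The concern.** When a participant answers the Myers index, ABS and STAI-X, the consent form has been read but no needle, real or sham, has been used. Disclosure can therefore have changed the answers; acupuncture type cannot. With random allocation, the acupuncture comparison on these scores has a true null hypothesis by design. The planned model nevertheless tests it and gives a p value below 0.05 the same label of significance as for de-qi, where an acupuncture effect is possible.

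At stake is a possible misreading of the results: a chance difference between the needle groups in consent-form credibility, belief in acupuncture or anxiety would appear in the results table as a significant acupuncture term. For these scores the only question the design can answer, and the one that matches the trial's objective, is whether the wording of the consent form changed them.

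**Working it through.** **1. Timing against model**

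| Score | When completed | Disclosure already given? | Needling already given? | Meaning of the acupuncture term |
|---|---|---|---|---|
| Myers index | Day 1, step 2 | yes | no | none |
| ABS | Day 1, step 2 | yes | no | none |
| STAI-X | Day 1, step 2 | yes | no | none |
| De-qi | after each session | yes | yes | valid |
| Acupuncture credibility test | Day 3, after the session | yes | yes | valid |

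Section 2.3.9 applies the same model to all five rows.

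**2. Inputs**
- Level 0.05 for each test (section 2.3.9); no adjustment for the number of tests is stated there.
- Sample size (section 2.2.4): 80 participants with 10% dropout gives 80 / (1 − 0.10) = 88.9, rounded up to 89. This reproduces the stated recruitment figure.
- Cell size: 80 / 4 = 20, or 22 if nearly all 89 are analysed (89 / 4 = 22.25). Equal groups are an assumption, because no allocation ratio is given.
- One score per scale: an assumption.
- Correlation between the three scores: not given, so taken over a range of 0 to 0.6.

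**3. Acupuncture term only, as the factors are worded**

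Three tests with a true null, independent scores: 1 − 0.95³ = 1 − 0.8574 = 0.143, so 14.3%. The expected number of false results is 3 × 0.05 = 0.15.

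**4. Acupuncture term plus interaction (assumed)**

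Six tests: 1 − 0.95⁶ = 1 − 0.7351 = 0.265, so 26.5%. The expected number is 6 × 0.05 = 0.30.

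**5. Check by simulation**

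A 2×2 ANOVA was simulated 20,000 times per setting, with three scores and no acupuncture or interaction effect. The entries are the chance of at least one false result.

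| Per cell | Correlation | Acupuncture only | Acupuncture or interaction |
|---|---|---|---|
| 20 | 0 | 14.2% | 26.6% |
| 20 | 0.3 | 13.6% | 25.4% |
| 20 | 0.6 | 11.8% | 22.6% |
| 22 | 0 | 14.7% | 26.7% |
| 22 | 0.3 | 13.4% | 25.2% |
| 22 | 0.6 | 12.1% | 22.2% |

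Each single test rejects at about 5%, as it should; the fault is that the question has no content. Adding a true disclosure effect of 0.5 SD (20 per cell, correlation 0.3) left the rates essentially unchanged: 13.8% for acupuncture only and 25.0% with the interaction.

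**6. After the change**

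If only disclosure is tested on these three scores, no acupuncture or interaction test remains, so this source of false results disappears. The disclosure comparison stays.

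**The case against.** The strongest reply is that little harm follows. Keeping both design factors leaves the disclosure test valid and costs at most two residual degrees of freedom: with 80 analysed, 80 − 4 = 76 against 80 − 2 = 78. The main outcomes (PPT, VAS, blinding index) are untouched. Section 2.2.4 calls the study hypothesis-generating and exploratory, so a familywise error rate over secondary questionnaires is a weak measure of damage. A reader who knows the schedule would discount an acupuncture effect on consent-form credibility. All of this stands, and it sets the weight of the point at minor. It does not give the acupuncture term a meaning for these scores.

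A reader might also infer more than the protocol supports:

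- *That the plan tests an interaction on these scores.* Section 2.3.9 names only the two factors. An interaction is usual in a 2×2 ANOVA, but it is an inference, so 14.3% is the figure that follows from the wording and 22–27% is conditional.
- *That a significant acupuncture term could only be chance.* This is true of everyone randomised. The analysed set is smaller: section 2.3.4 has participants told their acupuncture type on Day 3, before they are asked to consent to use of their data, and those who decline are dropped. Section 2.2.2 allows other withdrawals. Exclusion related to arm could create a difference. It would be selection, still not an effect of needling.
- *That the plan hides the disclosure effect, or treats these scores as baseline checks or covariates.* It does neither. Disclosure is named as a factor for these scores, and section 2.3.9 mentions no covariate adjustment.
- *That the plan commits to reporting such a result as caused by acupuncture.* It says only that p below 0.05 counts as statistically significant.
- *A share of all planned score tests, or a higher rate from separate state and trait anxiety scores.* Either would need scoring rules that the protocol does not state.

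**Conclusion.** The point holds as a minor correction. The protocol names the scores, the factors and the threshold, and for three of the five scores that rule conflicts with its own schedule. It is therefore something the document fixes badly, not a detail left to an analysis plan. The acupuncture term on the Myers index, ABS and STAI-X cannot estimate an effect of needling; a significant value would be chance or selection after debriefing.

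The chance of at least one such false result is 14.3% for independent scores (11.8–14.7% in simulation), or about 22–27% if the interaction is also tested. These figures assume one score per scale, equal groups, correlations between 0 and 0.6, and no exclusion related to arm. They also assume that the acupuncture allocation does not influence the screening answers; section 2.3.5 does not say when the unblinded practitioner learns it. The disclosure comparison on these scores, and the two-way ANOVA of de-qi and the acupuncture credibility test, are sound in this respect.

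**What to change.** In section 2.3.9, split the sentence on the five scores by timing.

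- **Myers index, ABS, STAI-X (before needling):** compare full with partial disclosure only, reporting the mean difference with its 95% confidence interval and presenting it as an effect of the consent form. Describe the four groups without tests, as the same section already does for demographic data.
- **De-qi and acupuncture credibility test (after needling):** keep the two-way ANOVA with both factors.

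The cost is one sentence of analysis wording. No data collection changes, there are fewer tests, and no valid comparison is lost.
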